## Results

Development of *Drinks*:Ration is complete. Owing to the lockdown as a result of COVID-19, the RCT will start in October 2020. As participants can start at different timepoints, we aim to complete all data collection by October 2021. The results of this study will be communicated via publication.

## Discussion

Alcohol misuse is a persistent problem in the UK AF, with estimates forecasting that more than 50% of those who have left the AF meet the criteria for hazardous alcohol use. This is almost double that of the general population [65]. New and innovative modes of delivery and digital interventions are required to meet this demand [66]. At present, there are no smartphone-based alcohol interventions targeted toward the AF to reduce alcohol misuse, with estimates indicating that more than 50% of veterans misuse alcohol use [3]. Therefore, we have developed a theory-driven and user-centered smartphone app, which may help fill this gap in treatment. However, its efficacy, usability, and functionality need to be ascertained in a fully powered RCT. This study protocol describes the design of an RCT to determine the efficacy of *Drinks*:Ration within a treatment-seeking veteran population.

To our knowledge, this is one of the first studies to examine the efficacy of a smartphone app to reduce hazardous/harmful alcohol consumption in a treatment-seeking veteran population that has been developed based on empirical evidence, development guidelines, and co-design. Although this study uses a veteran sample recruited from Combat Stress, it is expected that the findings will be generalizable to the wider veteran community, as Combat Stress is a countrywide organization.

Previous research has shown that veteran alcohol misuse is often highly comorbid with other mental health conditions, which has been shown to have a negative impact on health treatment utilization and that veterans attend fewer health appointments [11]. The use of a smartphone app combined with personalized messaging and formative feedback may provide a cost-effective strategy to deal with the barriers to improving drinking behaviors and increasing mental health care adherence in the UK AF community. These proposed methods may build self-efficacy and promote behavior change in reducing alcohol intake. A novel aspect of this study, which has the potential to improve health care engagement and utilization, is the use of push notifications combined with SMS text messages to support behavior change. To our knowledge, this is one of the first large trials of a text messaging intervention to promote reductions in alcohol consumption in the AF community.

A key strength of this study is the collaboration between the charitable sector, academia, and the UK AF, which has enabled the development of *Drinks*:Ration. A further strength includes remote delivery via smartphones, so that there will be no issues with availability or geographical limitations for participants. The app can also be used on iOS and Android devices. However, our app requires an active data connection for the app to function when logging questionnaires to generate normative feedback. This is to operate the personalization algorithms. We anticipate several challenges in this study. First, our ability to recruit and retain sufficient number of participants to power our analysis, as it is known that many of those who have alcohol-related problems are reluctant to seek help to ameliorate their problems. We planned our recruitment approach following the best practice to mitigate this issue. Further, the app has been designed to promote its active use, with frequent reminders, which is expected to promote adherence to the app. Second, we expect that some participants may encounter technical issues related to the app (eg, unable to log drinks and unable to receive notifications) or the mobile device. To mitigate potential technical or mobile device issues, we have undertaken extensive testing across a range of popular mobile devices and we will allow participants to provide in-app feedback that will be regularly monitored by the research team. Third, the impact of COVID-19 on the study, participant recruitment, engagement, or attrition is unknown. The research team will monitor the situation and handle issues as they arise. Finally, we acknowledge that our sample comprises participants who may be undergoing active treatment. To mitigate this risk, we will undertake statistical analyses to compare the control and intervention arms, and, where identified, these differences will be highlighted when reporting the trial.

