### Study Sample

Participants may have been, or are presently, receiving treatment through Combat Stress. Treatment offered via Combat Stress is for depression, anxiety, and PTSD. However, Combat Stress does not offer alcohol treatment services. The eligibility criteria are as follows:

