#### Exclusion Criteria

Participants will be excluded if they are listed as being *red* risk by Combat Stress, which is determined by the clinical team following an initial assessment and is based on a traffic light system to assess risk, where red indicates an immediate high risk to the individual and/or others. *Red* risk is applied independently of the research team and is used only where participation in the study could impact clinical treatment. The exclusion applies only during the contact list data extraction. Participants will be excluded if they do not have a mobile phone or have not given the Combat Stress consent for contact for research purposes.

A power calculation was performed based on previously reported data from Combat Stress [11,46]. This study requires a sample of 37 participants in each arm, with an 80% power to detect with a probability of 5% mean change in alcohol consumption of 4 UK units (approximately 40 g of alcohol per week, 10 g per unit) between control and intervention arms, at 3-month follow-up (day 84). Four units have been selected based on these 2 criteria: (1) reductions observed in similar studies [4,8,22,24,47] and (2) reductions observed in the feasibility trial of *Drinks*:Ration, which found a 7 UK-unit decrease at week 4. We aim to invite a minimum of 620 veterans to participate in the study to account for a 30% acceptance of invitation and 40% attrition rate.

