### Recruitment

This study will recruit participants through Combat Stress (established in 1919), a third-sector charitable organization that provides mental health services, including substance misuse to UK veterans. It is the largest military charity in the United Kingdom in terms of the number of individuals treated, providing both inpatient and outpatient secondary mental health services to veterans and specializing in PTSD. Since 2011, Combat Stress has been funded by the NHS in the United Kingdom to provide a national specialist PTSD clinical service for veterans [48]. Combat Stress facilitates access to eligible participants and jointly with King’s College London oversees any risks that arise as a result of participation in the study. It is important to note that although this study uses a sample of veterans from Combat Stress, it is hoped that *Drinks*:Ration will be useful for the wider veteran community.

Potential participant contact details (postal address and/or email if available) will be extracted from the Combat Stress Patient Management System for those who meet the study eligibility criteria and who have provided consent to be contacted for research purposes. Only those who have had contact with Combat Stress over a 2-year period between January 1, 2018, and December 31, 2019, will be contacted. It is estimated that about 3000 patients with Combat Stress are eligible to be contacted by the research team.

Where contact details are available, eligible participants will be invited to take part via email in the first instance. The first contact will include an explanation of the study, link to the participant information sheet, and instructions on how to download *Drinks*:Ration using a unique quick response (QR) code. Once participants have downloaded the app, they will be invited to report alcohol consumption using TLFB for alcohol consumption [43] for the last 7 days and confirm the military serving status (to validate eligibility). Those meeting the study eligibility criteria will be invited to register an account and complete the baseline questionnaire (day 0).

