### Randomization and Blinding

Randomization occurs when a QR code is generated and a unique proxy identifier and participant gender are assigned. At this point, participants are automatically randomized to receive the control or intervention arm (see the Intervention section) and are blinded. Block randomization of size 2 will be used to ensure equal gender distribution across both conditions. The randomization procedure is carried out automatically by the *Drinks*:Ration platform with no human involvement, except to provide a proxy identifier and gender. The research team will be blinded to the randomization of the participant, except for DL, who led the development and will manage the *Drinks*:Ration app throughout the study.

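### Comparing the arms and highlighting differences does not deal with active treatment; day-0 treatment status should be a prespecified covariate whatever the comparison shows

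*Protocol article*

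**What the plan says.** The last of the challenges listed in the Discussion is that participants may be under active treatment. The stated response is: "we will undertake statistical analyses to compare the control and intervention arms, and, where identified, these differences will be highlighted when reporting the trial". Study Sample confirms that past and current patients of the charity are both eligible.

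Under Randomization and Blinding the only balancing factor is gender: "Block randomization of size 2 will be used to ensure equal gender distribution across both conditions". The Statistical and Data Analysis Plan section describes between-arm t tests and chi-square tests, placed at follow-up, with a threshold of 0.05. It names a repeated-measures mixed model for the primary outcome.

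On what the charity's care contains, two sections differ. Study Sample says: "Combat Stress does not offer alcohol treatment services". Recruitment describes the same charity as one that "provides mental health services, including substance misuse to UK veterans".

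**The concern.** The protocol identifies a factor that could plausibly influence drinking over the follow-up period, then offers a remedy that cannot act on the estimate. If the arms differ on treatment status, a sentence in the report tells the reader so, but the contrast between arms is unchanged. If the comparison finds nothing, that does not show balance, because a comparison of this size misses moderate gaps.

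Timing adds a second difficulty. The only between-arm tests that the analysis section describes are at follow-up, and the Discussion itself hopes that the messaging will raise engagement with health care. Treatment status measured then may partly be a result of the intervention, so a difference could not be read as a baseline imbalance.

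The disagreement over substance misuse services matters because it decides whether concurrent care might act on alcohol intake directly or only through depression, anxiety and PTSD.

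**Working it through.** **Inputs from the documents** (sample-size paragraph under Exclusion Criteria): "This study requires a sample of 37 participants in each arm, with an 80% power to detect" and "with a probability of 5% mean change in alcohol consumption of 4 UK units"; 620 invitations "to account for a 30% acceptance of invitation and 40% attrition rate".

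**Inputs that are assumed**, because the documents do not give them: 50% of participants in current treatment; an effect of current treatment on the *change* in weekly drinking of 2, 4 or 7 units; a two-sided test.

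**1. The plan's own figure.** The 37 per arm cannot be reproduced, because only the source of the variability is given: "A power calculation was performed based on previously reported data from Combat Stress". Working backwards, SE = 4/(1.960 + 0.842) = 1.43 units, so the implied SD of change is 1.43 × √(37/2) ≈ 6.14 units.

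**2. Which sample size applies.** The 37 per arm is the number needed at day 84. A baseline comparison would use everyone enrolled: 37/0.6 ≈ 62 per arm from the stated attrition, or 620 × 0.30/2 = 93 per arm from the invitation target. All three are shown.

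**3. How often a gap arises, and how large it must be to be flagged.** The chance of a gap is the exact probability that two independent Binomial(n, 0.5) proportions differ by at least 0.15. The critical gap is 1.96 × √(2 × 0.5 × 0.5/n). Power is by exact enumeration of the uncorrected chi-square test.

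| Per arm | Chance of gap ≥ 15 points | Smallest gap flagged at 5% | Power, 40% v 60% |
|---|---|---|---|
| 37 | 20% | 22.8 points | 40% |
| 62 | 9% | 17.6 points | 64% |
| 93 | 5% | 14.4 points | 78% |

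The power column shows how sensitive such a test is to an underlying difference. Randomization rules out an underlying difference, so the critical gap is the more direct measure. At 37 or 62 per arm a 15-point gap is not flagged. At 93 it is flagged, and then only mentioned in the report.

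**4. Effect of a gap on the contrast.** Shift = gap × effect of treatment on the change in drinking.

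- 2 units: 0.15 × 2 = 0.30 units; 0.30/4 = 8% of the target
- 4 units: 0.15 × 4 = 0.60 units; 0.60/4 = 15%
- 7 units: 0.15 × 7 = 1.05 units; 1.05/4 = 26%

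Against the SE of 1.43 these are 0.21, 0.42 and 0.73 standard errors.

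**5. Precision given up by not adjusting.** With half in treatment, status explains 0.25 × effect²/6.14² of the variance of change: 0.25 × 4/37.7 = 3%, 0.25 × 16/37.7 = 11%, 0.25 × 49/37.7 = 32%. Adjustment would reduce the SE by a factor √(1 − share), that is by about 1%, 5% or 18%. This uses the implied SD of 6.14.

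**The case against.** The case on the other side has several sound parts.

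- *A reader might infer that the primary result will be confounded or biased.* The documents do not support that. Allocation is random, so any imbalance in treatment status at baseline is chance, the unadjusted estimate is unbiased on average, and the test keeps its 5% level over repeated randomizations.
- *A reader might infer that the comparison can never detect an imbalance.* That is too strong. Gaps of about 23 points or more are flagged at 37 per arm, and power for 40% v 60% reaches 78% at 93 per arm.
- *The size of the effect is undocumented.* No section says how far concurrent care alters drinking. Because the outcome is change from baseline, a stable difference in level between current and past patients largely cancels, and only a different change after day 0 shifts the contrast. At 2 units the shift is small.
- *The covariate list belongs to the analysis plan.* This is a condensed article, and the absence of an adjustment term is no error. The Discussion sentence does not say that comparison is the only step, nor does it name significance tests or a time point. Reading it as testing at follow-up is an inference from the analysis section.

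What these arguments leave standing is the stated remedy. The protocol offers compare-and-highlight as mitigation, and that would not mitigate anything even if a separate plan adds a covariate. Nor does the text on services show that the charity does treat alcohol misuse. It shows only that two sections disagree.

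**Conclusion.** The point holds as a weakness in a stated method, not as a threat to the validity of the randomized comparison. Highlighting cannot correct the estimate, and the result of a between-arm comparison should not decide how a named, plausibly prognostic factor is handled.

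The size depends on assumptions. With half the sample in treatment, a gap of 15 points or more is roughly a 1-in-5 event at 37 per arm, 1-in-11 at 62 and 1-in-20 at 93. Such a gap of 15 points moves the contrast by 0.30 to 1.05 units over the assumed range of effects. The lower end is of little consequence; the upper end is about a quarter of the target difference. Whether a relevant imbalance will occur cannot be known from the documents, which is a reason to settle the handling beforehand.

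The disagreement between Study Sample and Recruitment is established by the text alone and is secondary to the covariate.

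**What to change.** Replace the mitigation sentence in the Discussion, and carry the same statement into the analysis section, with wording such as:

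> Treatment status at day 0 (current or past) is a prespecified covariate in the primary and secondary mixed models, regardless of any between-arm comparison. Its distribution is described by arm at baseline without significance tests. Treatment status measured at follow-up is not used for adjustment.

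One detail needs care. If baseline drinking is modelled as one of the repeated outcomes, status should enter with its interaction with visit. A main effect alone adjusts the level and leaves the contrast in change largely untouched. If baseline drinking is a covariate instead, a main effect suffices.

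Reconcile Study Sample and Recruitment on whether the charity's services include alcohol or substance misuse care, and let the day-0 item record any current alcohol treatment.

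The cost is one degree of freedom, a second if the visit interaction is needed, and one baseline question if treatment status is not already held. The planned comparison needs that information anyway.

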## Appendix

Multimedia Appendix 1 Behaviour Change Technique assignment to each *Drinks*:Ration component.

Multimedia Appendix 2 Questionnaire mark-up.

Multimedia Appendix 3 Drinks Menu Alcohol Unit Assignment.

## Abbreviations

AF: armed forces
AUDIT: Alcohol Use Disorders Identification Test
BCT: behavior change technique
MAUQ: mHealth App Usability Questionnaire
NHS: National Health Service
NIHR: National Institute for Health Research
PTSD: posttraumatic stress disorder
QR: quick response
RCT: randomized controlled trial
TLFB: Timeline Follow-back for alcohol consumption
WHOQOL-BREF: World Health Organization Quality of Life-BREF
